##### **SI UNITS**

$$\text{Creatinine Clearance (mL/sec)} = \frac{(140 - \text{age}) \times \text{Body Weight (kg)}}{72 \times \text{Serum Creatinine (}\mu\text{mol/L)} \times 0.6786}$$

$$\text{Female CRCL} = \text{Male CRCL} \times 0.85$$

##### **CONVERSION FACTOR FOR CRCL**

$$\text{Conventional units (mL/min)} = \text{SI units (mL/sec)} / 0.0167$$

$$\text{SI units (mL/sec)} = \text{Conventional units (mL/min)} \times 0.0167$$

##### **CONVERSION FACTOR FOR SERUM CREATININE**

$$\text{Conventional units (mg/dL)} = \text{SI units (}\mu\text{mol/L)} / 88.4$$

$$\text{SI units (}\mu\text{mol/L)} = \text{Conventional units (mg/dL)} \times 88.4$$

## Appendix D

### Child–Pugh Classification of Severity of Liver Disease

**Table D1**  
Child–Pugh Scoring on Select Parameters

| Clinical and biochemical measurements                          | Points Scored for Increasing Abnormality |         |          |
|----------------------------------------------------------------|------------------------------------------|---------|----------|
|                                                                | 1                                        | 2       | 3        |
| Encephalopathy (grade) a                            | None                                     | 1 or 2  | 3 or 4   |
| Ascites b                                           | Absent                                   | Slight  | Moderate |
| Bilirubin (mg/100 mL)                                          | < 2                                      | 2–3     | > 3      |
| Albumin (g/100 mL)                                             | > 3.5                                    | 2.8–3.5 | < 2.8    |
| Prothrombin time (International Normalized Ratio) c | < 1.7                                    | 1.7–2.3 | > 2.3    |

Note: With increasing abnormality of each of the five parameters measured, 1, 2, or 3 points are scored. Grade A: 5 or 6 points. Grade B: 7–9 points. Grade C: 10–15 points.

a According to grading of Trey, Burns, and Saunders (1966).

b As determined by physical examination alone.

c Prothrombin time results should be reported and used for calculations only as International Normalized Ratios because of variations in the methods used and reference ranges for controls (expressed in seconds).

## **Appendix E**

### **Package Inserts for Boceprevir, Pegasys, and Copegus**

[http://www.merck.com/product/usa/pi\\_circulars/v/victrelis/victrelis\\_pi.pdf](http://www.merck.com/product/usa/pi_circulars/v/victrelis/victrelis_pi.pdf)

[http://www.ema.europa.eu/docs/en\\_GB/document\\_library/EPAR\\_-\\_Product\\_Information/human/002332/WC500109786.pdf](http://www.ema.europa.eu/docs/en_GB/document_library/EPAR_-_Product_Information/human/002332/WC500109786.pdf)

<http://www.gene.com/gene/products/information/pegasys/pdf/pi.pdf>

[http://www.gene.com/gene/products/information/pegasys/pdf/Copegus\\_pi.pdf](http://www.gene.com/gene/products/information/pegasys/pdf/Copegus_pi.pdf)

## **Appendix F**

### **Dose Modifications, Interruptions, and Delays**

The intention of the protocol is for patients demonstrating a response to therapy to remain on study drug until the completion of the study treatment period. However, it is possible that some patients will encounter transient or prolonged AEs at some juncture during their participation in the trial necessitating test drug dose adjustment. To minimize the effects of these modifications on the eventual evaluation of the safety, tolerability, and efficacy of test drug regimens, the principles in the following sections will be used to adjust the dose of test drugs.

#### **RO5024048 AND BOCEPREVIR DOSE INTERRUPTION OR DISCONTINUATION**

No dose modifications will be allowed for RO5024048 or boceprevir.

RO5024048 must be discontinued immediately and the Sponsor's Medical Monitor contacted within 24 hours if any of the following are confirmed and **considered related** to the study drug:

- Creatinine clearance:  $\geq 35\%$  decrease from baseline or  $< 60$  mL/min ( $< 1.00$  mL/sec) confirmed by repeat test, preferably within 1 week
- Any clinically significant Grade 4 laboratory abnormality confirmed by repeat test, preferably within 1 week, unless otherwise defined
- Any SAE assessed as related to RO5024048

It is important that patients receive the full dose of RO5024048 and/or boceprevir. However, moderate or severe adverse reactions (clinical and/or laboratory) may necessitate dose interruption or discontinuation of RO5024048 and/or boceprevir.

If a dose of RO5024048 or boceprevir is missed and the patient remembers the same day, the patient must take the missed dose if the next scheduled dose is more than 4 hours away. The patient should not take two doses at the same time or within 4 hours of each other.

Patients who discontinue all study drugs should return for the PW visit as soon as possible after their last dose of study medication, according to [Appendix A](#). Patients who prematurely discontinue from the study will be assessed for safety and efficacy at 4 and 12 weeks after the last dose of study treatment. In addition, patients who prematurely discontinue and have unquantifiable HCV RNA will be assessed for efficacy at 12 weeks after the last dose of study treatment as long as they remain HCV RNA unquantifiable at their last assessment.

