### **3.4.1.2      Secondary Efficacy Outcome Measures**

For the following measures, which are HCV RNA response outcomes, response is defined as an unquantifiable (less than the LLOQ [ $< 25$  IU/mL]) serum HCV RNA:

- Hepatitis C virus RNA response outcome at clinic visits over time
- Sustained virologic response 24 weeks after treatment (SVR-24 actual) outcome, defined as the HCV RNA response outcome  $\geq 20$  weeks after the last day of study drug administration
- Sustained virologic response 4 weeks after treatment (SVR-4 actual) outcome, defined as the HCV RNA response outcome within 2–8 weeks after the last day of study drug administration
- Hepatitis C virus ( $\log_{10}$  IU/mL) change from baseline to Week 24
- Occurrence of documented DAA resistance

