#### **4.5.2.3 Assessments at Study Completion/Early Termination Visit**

Any patient who prematurely discontinues all study drugs should return for the PW Visit as soon as possible after the last dose of study medication. Additional requirements exist for patients who have unquantifiable HCV RNA levels at the time of premature study drug discontinuation (see [Appendix A](#)).

- If a patient stops Pegasys, all study medications must be discontinued.
- If a patient stops one DAA (either RO5024048 or boceprevir), the patient may remain on the other DAA (either RO5024048 or boceprevir) plus Pegasys/Copegus.
- If both RO5024048 and boceprevir are stopped, the patient may remain on Pegasys/Copegus.
- If a patient stops Copegus, all study medications must be discontinued.
- Patients should not be treated with a single DAA (either RO5024048 or boceprevir) and Pegasys or with Pegasys monotherapy.
- In other circumstances, the investigator should consult with the Sponsor.

See [Appendix A](#) for the Schedule of Assessments performed at the Study Completion/Early Termination Visit.

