- A urine protein/creatinine ratio  $\geq 0.5$  (56.51 mg/mmol) and greater than the baseline value confirmed by repeat test, preferably within 1 week (see [Appendix H](#))

Refer to [Appendix F](#) and [G](#) for more details on stopping rules and for additional guidance on the management of specific AEs and laboratory abnormalities.

Patients who discontinue study drug prematurely will be asked to return to the clinic for a Study Completion/Early Termination Visit (see Section [4.5.2.3](#)) and may undergo follow-up assessments (see Section [4.5.2.4](#)). The primary reason for premature study drug discontinuation should be documented on the appropriate eCRF. Patients who discontinue study drug prematurely will not be replaced.

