## Appendix A (cont'd)

### Schedule of Assessments

---

Ab = antibody; AE = adverse event; AFP = alpha-fetoprotein; AMA = antimitochondrial Ab; ANA = antinuclear Ab; ASMA = antismooth muscle Ab; AT = antitrypsin; CK = creatine kinase; CRCL = creatinine clearance; CT = computerized tomography; HAV = hepatitis A virus; HBsAg = hepatitis B surface antigen; HCV = hepatitis C virus; Hgb = hemoglobin; INR = International Normalized Ratio; Serum IP-10 = interferon gamma-induced protein 10kDa; MCH = mean corpuscular hemoglobin; MCHC = mean corpuscular hemoglobin concentration; MCV = mean corpuscular volume; MRI = magnetic resonance imaging; PD = pharmacodynamic; PK = pharmacokinetic; PT = prothrombin time; PW = Premature Withdrawal Visit; RCR = Roche Clinical Repository; SAE = serious adverse event; TSH = thyroid-stimulating hormone.

- a Assessments to be performed 4, 12, and 24 weeks after the last dose of study treatment in all patients who completed treatment. Patients who prematurely discontinue from the study will be assessed for safety and efficacy at 4, 12, *and* 24 weeks after the last dose of study treatment.
- b All patients who prematurely withdraw are recommended to complete the PW Visit as soon as possible after the last dose of study medication and proceed with treatment-free follow up.
- c Includes height and weight.
- d Repeat if any change in medical condition is noted since the screening examination.
- e Physical examination only.
- f Only for patients with pre-existing pulmonary disease or current respiratory symptoms.
- g All patients must have a liver biopsy or fibroscan assessment. Fibroscan must be completed within 12 calendar months of the first dose (an elasticity score of  $\geq 12.5$  kPa will be used to designate incomplete/transition to cirrhosis (i.e., "cirrhotic") a score of  $\geq 9.5$  kPa but  $< 12.5$  kPa will require a patient to undergo a liver biopsy to determine whether he/she is designated as "cirrhotic" or "non-cirrhotic").
- h Ultrasound within 6 months prior to randomization. If a patient has had a CT or MRI scan within the 6-month period that includes cuts of the entire liver, these assessments may be substituted for an ultrasound as the liver imaging procedure. Endoscopy within 2 years prior to randomization.

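### Appendix F and Appendix A give different follow-up schedules for early discontinuers, and a site that follows Appendix F may not collect the sample that SVR-24 needs

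*Protocol*

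**What the plan says.** **Appendix F**, under dose interruption or discontinuation of RO5024048 and boceprevir, states that patients who discontinue prematurely "will be assessed for safety and efficacy at 4 and 12 weeks after the last dose of study treatment". It then adds a rule for those with unquantifiable HCV RNA, who "will be assessed for efficacy at 12 weeks after the last dose of study treatment as long as they remain HCV RNA unquantifiable", judged by the most recent result.

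**Appendix A, footnote a**, addresses the same patients in almost the same sentence: "Patients who prematurely discontinue from the study will be assessed for safety and efficacy at 4, 12, *and* 24 weeks", counted from the last dose. Footnote b recommends that premature withdrawals attend the withdrawal visit "as soon as possible after the last dose of study medication and proceed with treatment-free follow up".

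**Section 4.5.2.3** says "Additional requirements exist for patients who have unquantifiable HCV RNA levels at the time of premature study drug discontinuation" and refers the reader to Appendix A for them. **Section 4.6.1.1** says that patients who stop study drug early "may undergo follow-up assessments", and refers to Section 4.5.2.4, which in turn refers to Appendix A.

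**Section 3.4.1.2** lists "Sustained virologic response 24 weeks after treatment (SVR-24 actual) outcome, defined as the HCV RNA response outcome" at 20 weeks or more after the last day of study drug. SVR-24 is a secondary objective for both groups (Section 2.2), and Section 6.4 analyses it in everyone randomized who took at least one dose. Early discontinuers are therefore part of that analysis.

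**The concern.** Two current, operative passages prescribe different visits for the same patients. The one that omits week 24 sits in the appendix a site is likely to open when a patient stops drug. The Appendix F sentence on unquantifiable patients is introduced as an addition but names only the 12-week assessment already listed, so it does not close the gap. The pointer in Section 4.5.2.3 does not close it either: none of footnotes a to y in Appendix A sets out a requirement specific to these patients.

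At stake is SVR-24 in patients who stop early while responding. Without a sample at 20 weeks or later, their outcome has to be imputed or the patients left out. With 30 patients per arm, one to three such cases move the estimate visibly. A sample not taken in the window cannot be recovered afterwards.

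**Working it through.** **1. Visits against endpoint windows** (weeks after last dose)

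| | Appendix F | Appendix A, footnote a |
|---|---|---|
| Visits named | 4, 12 | 4, 12, 24 |
| SVR-12 window, 8–20 weeks (Section 3.4.1.1) | week 12 is inside | week 12 is inside |
| SVR-24 window, 20 weeks or later (Section 3.4.1.2) | no visit | week 24 is inside |

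The last visit named in Appendix F falls 20 − 12 = 8 weeks before the SVR-24 window opens. The primary endpoint can be collected under either schedule.

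**2. Which text governs?**

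- Section 4.5.1 says patients are assessed according to the schedule in Appendix A.
- Section 4.5.2.4 sends follow-up assessments to Appendix A, and Section 4.6.1.1 sends early discontinuers to Section 4.5.2.4.
- Footnote b leads on to treatment-free follow-up, where HCV RNA is marked at weeks 4, 12 and 24. It is worded as a recommendation.
- Appendix F cites Appendix A only for the withdrawal visit. Its follow-up sentences stand on their own.

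The balance favours Appendix A, but there is no statement of precedence.

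**3. A yardstick from the plan.** Section 6.1 gives a 90% confidence interval of ±15% for 30 patients per group at response rates of 45%–55%. The normal-approximation half-width is 1.645 × √(p(1 − p)/30). It gives 14.9% at p = 0.45, 15.0% at p = 0.50 and 14.9% at p = 0.55, so the plan's figure reproduces. It is not itself in question.

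**4. Illustration of size.** The documents give no discontinuation rate. Assumptions: true SVR-24 is 15/30 = 50% in an arm; d patients stop early and have no week-24 sample; k of these d are true responders.

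| d | k | Missing = failure: (15 − k)/30 | Observed only: (15 − k)/(30 − d) | 90% half-width with n = 30 − d, p = 0.5 |
|---|---|---|---|---|
| 3 | 1 | 14/30 = 46.7% (−3.3) | 14/27 = 51.9% (+1.9) | 15.8% |
| 6 | 2 | 13/30 = 43.3% (−6.7) | 13/24 = 54.2% (+4.2) | 16.8% |
| 9 | 3 | 12/30 = 40.0% (−10.0) | 12/21 = 57.1% (+7.1) | 17.9% |

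The observed-only column drops every early discontinuer. If those already quantifiable at week 12 were instead kept as failures and only the k responders dropped, the estimate would be (15 − k)/(30 − k): 14/29 = 48.3%, 13/28 = 46.4% or 12/27 = 44.4%, which is low again. The direction therefore depends on the missing-data rule, which may properly be left to the analysis plan. The shift itself arises from the missing sample.

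**The case against.** The strongest reply is that this is stale wording in a dosing appendix. Three parts of the protocol lead to Appendix A, the visit table there contains week 24, and a site working from the visit schedule will take the sample. That stands as the more likely reading. It does not remove the conflict, because Appendix F uses directive language and nothing ranks the two.

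Several stronger readings are tempting, and the documents do not support them.

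- *SVR-24 can never be observed in early discontinuers.* Appendix F names no visit after week 12, but it does not forbid one. Loss occurs only where a site follows Appendix F in place of Appendix A.
- *The bias could reach 15 percentage points.* One can get there by supposing that 30% stop early and half of those are unquantifiable: 0.30 × 30 × 1/2 = 4.5 patients, and 4.5/30 = 15%. Neither rate is in the protocol. The figure also needs every one of those patients to be a true SVR-24 responder at a site that skips week 24. Patients who relapse by week 12 are failures anyway and cause no bias when missing counts as failure.
- *The arms lose data unequally.* Group B is treated for 48 weeks against 24, so it has longer in which to stop early. No differential rate is given, and SVR-24 is estimated by group without formal testing (Section 6.4).
- *Resistance and safety follow-up are lost.* A week-24 visit would be missed at a site using Appendix F. However, Section 4.5.1.8 separately requires monitoring of resistant patients during follow-up, and Sections 5.5 and 5.6 continue adverse-event follow-up and reporting without relying on that visit.

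The permissive verb in Section 4.6.1.1 may simply allow for withdrawal of consent, after which Section 4.6.1.2 ends follow-up. It is not an error on its own.

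**Conclusion.** The concern holds as an internal contradiction in current text. Appendix F and Appendix A, footnote a, give different follow-up for the same patients, and the Section 4.5.2.3 pointer leads to requirements that are not there. A site that follows Appendix F may not collect the HCV RNA sample needed for SVR-24, a stated secondary objective. SVR-12 is untouched.

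The size cannot be established from the protocol. In the illustrated range of 1 to 3 true responders per arm of 30 without a sample, SVR-24 would read 3.3 to 10.0 points low with missing as failure, or 1.9 to 7.1 points high in observed patients only. Against a planned precision of ±15%, that is worth preventing but does not undermine the study. These figures assume a true rate of 50% and that the sample was not taken in any of the early discontinuers counted; they are not a prediction. The case for correction rests on the conflicting text and not on these numbers.

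**What to change.** Reconcile Appendix F, Appendix A (footnote a), Section 4.5.2.3 and Section 4.6.1.1 to one follow-up schedule for early discontinuers that includes a sample in the SVR-24 window:

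- In Appendix F, replace the two follow-up sentences with a reference to Appendix A, footnote a.
- In Section 4.5.2.3, delete the pointer to additional requirements, or write those requirements into Appendix A if any are intended.
- Optionally, align Section 4.6.1.1 by stating that follow-up takes place unless consent is withdrawn.

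No dose or treatment-stopping rule is touched. The cost is amendment wording and at most one visit, already in the schedule, for a few patients at sites that had been working from Appendix F. The change is useful only while those patients can still be sampled in the window.

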## Appendix F

### Dose Modifications, Interruptions, and Delays (cont.)

#### PEGASYS DOSE INTERRUPTIONS, DELAYS, AND MODIFICATIONS

If a Pegasys dose is delayed but eventually administered, the following guidelines should be used for the next scheduled dose(s).

##### **Dose delayed by 1 or 2 days**

Administer next dose on usual dosing day of the week (e.g., if Monday is the usual dosing day and the dose is delayed until Wednesday, the next dose may be administered as usual on Monday).

##### **Dose delayed by 3-5 days**

Administer subsequent doses every fifth or sixth day until the patient is back to his or her original schedule (e.g., if Monday is the usual dosing day and the dose is delayed until Saturday, the next dose should be administered on Thursday, the following dose on Tuesday, then the dose after that as usual on Monday).

##### **Dose delayed by 6 days**

Withhold the dose for that week, then continue on the usual schedule the following week (e.g., if Monday is the usual dosing day but the patient is not ready to be dosed until the following Sunday, the dose is considered to have been withheld and the next injection should be for the following week's dose on Monday).

##### **Dose delayed by $\geq 7$ days**

The investigator may reintroduce Pegasys at any time and, if necessary, dose the patient every fifth or sixth day until the patient resumes weekly dosing on his/her usual scheduled day.

Moderate or severe adverse reactions (clinical and/or laboratory) may require a dose reduction of Pegasys. Decremental reductions should be uniform across centers and patients. Toward this end, downward reductions should follow the guidelines shown in [Table F1](#).

**Table F1**  
General Pegasys Dose-Reduction Scheme

|                       |         |        |
|-----------------------|---------|--------|
| Full Pegasys dose     | 1.0 mL  | 180 µg |
| One-level reduction   | 0.75 mL | 135 µg |
| Two-level reduction   | 0.5 mL  | 90 µg  |
| Three-level reduction | 0.25 mL | 45 µg  |

## Appendix F

### Dose Modifications, Interruptions, and Delays (cont.)

Once a patient's dose has been reduced or withheld for an adverse reaction, the investigator may attempt to increase the dose back to or toward that which was originally assigned if the event has resolved or improved.

Specific dose adjustment guidelines for Pegasys are provided below for elevated serum ALT, depression (see [Table F2](#)), neutropenia (see [Table F3](#)), thrombocytopenia (see [Table F3](#)), and low Hgb (see [Table F4](#)).

#### **Dose Adjustments for Elevated Serum ALT**

Fluctuations in abnormalities of liver function tests are common in patients with CHC. As with other alfa IFNs, increases in ALT levels above baseline have been observed in patients treated with Pegasys, including patients with a virologic response.

In patients with progressive ALT increases above baseline, the dose of Pegasys should be reduced by one level. If ALT increases are progressive despite dose reduction or accompanied by increased bilirubin or evidence of hepatic decompensation, therapy should be immediately discontinued.

**Table F2**  
Guidelines for Modification or Discontinuation of Pegasys and for Scheduling Visits for Patients with Depression

| Depression Severity | Initial Management (4–8 weeks)                                                                     |                                                               | Depression                                                 |                                                                                                                                    |                                     |
|---------------------|----------------------------------------------------------------------------------------------------|---------------------------------------------------------------|------------------------------------------------------------|------------------------------------------------------------------------------------------------------------------------------------|-------------------------------------|
|                     | Dose Modification                                                                                  | Visit Schedule                                                | Remains Stable                                             | Improves                                                                                                                           | Worsens                             |
| Mild                | No change                                                                                          | Evaluate once weekly by visit and/or phone                    | Continue weekly visit schedule                             | Resume normal visit schedule                                                                                                       | (See moderate or severe depression) |
| Moderate            | Decrease Pegasys dose by one level adjustment (in some cases a two-level adjustment may be needed) | Evaluate once weekly (office visit at least every other week) | Consider psychiatric consultation. Continue reduced dosing | If symptoms improve and are stable for 4 weeks, may resume normal visit schedule. Continue reduced dosing or return to normal dose | (See severe depression)             |
| Severe              | Discontinue Pegasys permanently                                                                    | Obtain immediate psychiatric consultation                     | Psychiatric therapy necessary                              |                                                                                                                                    |                                     |

